## Abstract

**Background:**

The incidence of testicular germ cell tumors (TGCT), the most common cancer in men aged 15 to 45 years, has doubled over the last 30 years in developed countries. Reasons remain unclear but a role of environmental factors, especially during critical periods of development, is strongly suspected. Reliable data on environmental exposure during this critical time period are sparse. Little is known on whether it could be a combined effect of early and later-life exposures.

**Methods/Design:**

Our research aims to study the association between TGCT risk and pesticide exposures (domestic, occupational and environmental) during critical time periods of development and combined early and later-life exposures. The study design, developed during a 2-year pilot study, is a multicenter case–control study of 500 cases (ascertained through histology) and 1000 fertile/fecund controls recruited through 21 French ‘*Centres d’Etude et de Conservation des Œufs et de Sperme humain*’ (CECOS). Trained professional interviewers interview the subjects and their mothers by phone. Using a geographic information system developed and tested for application in this study design, environmental pesticides exposure assessment is based on life-time residential history. Occupational pesticides exposures are assessed by an industrial hygienist based on parents’ occupations and tasks. Exposures during the prenatal period, early childhood and puberty are focused. A blood sample is collected from each participant to assess genetic polymorphisms known to be associated with TGCT risk, as well as to explore gene-environment interactions.

**Discussion:**

The results of our study will contribute to better understanding the causes of TGCT and the rapid increase of its incidence. We explore the effect of combined early and later-life pesticides exposure from multiple sources, as well as potential gene-environment interactions that have until now been rarely studied for TGCT. Our design allows future pooled studies and the bio-bank allows additional genetic or toxicological analyses.

## Background

Testicular Germ Cell Tumors (TGCT, testicular cancer) represent the most frequent cancer in young men aged 15 to 45 years in developed countries with primarily Caucasian populations. TGCT incidence has been increasing throughout Europe over the last 30 years, including in France, where the annual incidence rate has doubled from 3.4/100 000 in 1980 to 7/100 000 in 2008 [1–3]. Large geographical variation in incidence rates exists between different European countries with West–east and North–south gradients [2, 4]. The reasons for such a phenomenon are still unclear but a role of environmental factors is strongly suspected. The rapid increase of TGCT incidence rates and the evolution of the incidence rate in migrant populations [5, 6] support this hypothesis. However, TGCT risk varies also by ethnicity (Caucasian men have a higher TGCT risk than men in Asian or African populations) [7], and familial history of TGCT is also known to be associated with an increased TGCT risk [8], supporting a potential role of genetic factors. It is estimated that 13% of TGCT have a genetic origin [8]. Individual factors have also been suggested to be associated with TGCT risk [9, 10] and several studies have suggested a positive association between a higher socioeconomic status and TGCT occurrence [11–13], although this relationship was not consistently found [14].

Given the peak incidence of TGCT in very young adults and the fact that TGCT has been shown to develop through carcinoma-in situ cells of fetal origin [15], the role of early exposures, in particular during the critical time windows when the reproductive tract develops has been hypothesized [16, 17]. The concept of the Testicular Dysgenesis Syndrome (TDS) proposes that an impaired development of fetal testes may lead to an increased risk of cryptorchidism, hypospadias, testicular cancer and decreased spermatogenesis [17, 18]. However, the TDS incidence in the general population is unknown and to what extent these disorders are actually biologically related through a fetal mechanism remains unresolved. Although the concept of TDS remains controversial [19, 20], the hypothesis of a pre-natal origin of TGCT and a role of in-utero or early childhood exposures to environmental factors in TGCT development remain widely accepted. A combined effect of prenatal, early and later-life (adolescence or adulthood) exposures has also been suggested [21], but has not been explored so far.

It is generally accepted that the development of TGCT is under endocrine control and exposures to chemicals with endocrine disrupting properties, including pesticides, have been suggested to be associated with an increased TGCT risk in epidemiological studies [21, 22]. So far, no appropriate animal models for TGCT exist, therefore our knowledge on factors involved in TGCT development is based on epidemiological research [23]. Reliable data on occupational or environmental risk factors during adulthood are sparse, and only a few studies have investigated parental exposures as a contributing factor to the risk of testicular cancer occurring 20–40 years later [24, 25]. Available studies were often limited by small sample size or by too broad exposure assessment. Furthermore, genetic polymorphisms might be involved in gene-environment interactions by increasing the susceptibility to the effect of endocrine disruptors [26], but these were rarely considered. Additional studies have investigated the place of residence (urban versus rural location), as a surrogate for pesticides exposure, but showed inconsistent results and none of these included the subject’s or parental residential history, or any detailed assessment to environmental pesticides exposure [27–30].

Accurate characterization of environmental pesticides exposure, especially in retrospective studies, is often difficult due to the lack of exposure data available at the individual level, and due to the inherent limitations of conventional epidemiological methods for this type of studies (e.g. recalls bias due to self-reported information). However, some studies have found a positive association between residential proximity to cultivated agricultural fields and pesticides concentrations in biological samples of residents [31–33]. Based on these observations, Geographic information systems (GIS) offer the opportunity to retrospectively assess agricultural pesticides exposures by collecting and analyzing historical environmental data over large areas [34, 35]. To our knowledge, GIS technology has not been applied to study environmental pesticide exposures in relation to TGCT risk.

The discordant findings and the limitations of available studies concerning TGCT risk factors underline the importance to conduct studies with sufficient statistical power to detect risks associated with exposures during critical windows of vulnerability, as well as combined perinatal and later life exposures. The current evidence further underscores the need for studies that can accurately characterize pesticides exposures from multiple sources (environmental, occupational and domestic). Therefore, we conducted a two year pilot study to develop a study design for the case–control study presented here, to compare the effectiveness of different approaches for cases’ , controls’ and mothers’ recruitment in the French context and to verify our ability to collect relevant data on exposures during subjects’ perinatal period (TESTEPERA project) [36]. Based on this pilot study, we chose a national, prospective, face-to-face recruitment. The results also confirmed our capacity to reconstruct cases’ and controls’ occupational and residential history and to accurately geocode most of the addresses (82%), including for early life periods.

### Objectives

Our case–control study aims to assess the impact of multisource pesticides exposure (domestic, occupational and environmental) during prenatal and early childhood periods on the risk to develop a TGCT during adulthood. The study is also designed to assess potential gene-environment interactions as well as the hypotheses of combined prenatal and later life exposure.

## Methods/Design

### Study design

The TESTIS study is a national, multicenter, prospective case–control study of 500 cases and 1000 controls (two groups of 500). Cases are recruited prospectively through the French centers for semen conservation (*Centres d’étude et de conservation d’oeufs et de sperme humain*, CECOS). Controls are recruited in CECOS and centers of assisted reproduction (group A), and regional maternities contiguous to the CECOS centers (group B). Twenty-one out of the 23 French CECOS, included in a national network (*Fédération Française des CECOS*), agreed to participate to the study (Besançon, Bordeaux, Caen, Clermont-Ferrand, Dijon, Grenoble, Lille, Lyon, Marseille, Montpellier, Nancy, Nice, Paris Tenon, Paris Jean Verdier, Paris Cochin, Reims, Rennes, Rouen, Strasbourg, Toulouse, Tours). The study protocol was approved by the French regulatory authorities and by the appropriate French ethics committees (*Comité consultatif sur le traitement de l'information en matière de recherche dans le domaine de la santé (CCTIRS)*; *Comité de protection des personnes (CPP); Agence nationale de sécurité du médicament et des produit de santé (ANSM)*). The study was registered at http://www.clinicaltrials.gov (NCT number: NCT02109926). Figure 1 shows the organization of the study for recruitment, data collection, biological sampling and samples conservation.

**Figure 1 Fig1:**
[figure not shown]
**Schematic organization of the recruitment and the data collection.** ART, Center for Assisted reproductive technology; CECOS, French center for semen conservation; CLB, Centre Léon Bérard; EDTA, Ethylene diamine tetra-acetic acid.

### Study population

The study population consists of men aged 18 to 44 years at date of diagnosis, born in metropolitan France, with a valid health insurance affiliation. Cases are men diagnosed with seminoma or non-seminoma TGCT (ascertained through histological report), and seen in one of the participating CECOS for sperm cryopreservation. Controls of group A are sperm donors or partners of infertile women having a normal sperm count (>39 million per ejaculate [37]). Controls of group B are partners of pregnant women hospitalized for a pathological pregnancy in the level III maternity (regional maternity) adjacent to the CECOS. Participants have to sign an informed consent form. Subjects unable to write and understand French language, as well as subjects presenting severe psychological or mental disorders, and subjects under legal guardianship are excluded. Controls with a history of cryptorchidism or of TGCT are also excluded. Two controls (one of each group) are matched to each case on age (±2 years) and the recruiting center.

Considering the incidence of TGCT and the CECOS activity, we estimate a 18-month duration to recruit all cases and controls. The recruitment is performed by physicians and/or midwives (investigators). A written permission is asked to cases and controls to contact their mothers (or the closest relative alive, if the mother is deceased or cannot be interviewed). Participants who sign the informed consent receive a document to prepare information prior to the phone interview, including: lifetime residential history, addresses of schools during childhood, parental occupation at subjects’ conception, birth information, and job history. Investigators propose to each case and control to participate in a blood sample collection. Information on subjects is recorded using a protected on-line study platform that generates a unique identification number for each participant. Cases and controls receive a financial compensation for their participation: 20 euros for completion of the interview and 40 euros for participation in both blood sampling and completion of the interview.

The Principal investigator (PI) contacts case and control mothers (or closest relative alive) upon written permission of cases and controls. Subjects are asked to inform their mother/relative beforehand. Mails include an information letter, a consent form (to be returned using an enclosed pre-paid envelope) and a document to prepare information on residential and job history prior to the interview. Mothers are registered on the same internet platform after the reception of the signed consent form. In absence of any response, up to three phone reminders are done, at two-week intervals.

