**Table 2 Tab2:** **Main advantages and weaknesses of the two control groups**

	Advantages	Weaknesses
Control Group A *(sperm donators & fertile partners of infertile woman)*	- Direct access to the subject (face to face recruitment & blood sampling)	- Older than cases/difficult to recruit subjects below 25 years old
	- More concerned by the topic/good participation rate	- Live with infertile woman/more exposed to reproductive toxicant than general population?
	- Sperm count available	
	- Regional recruitment	
Control Group B *(partners of pregnant woman hospitalized for pathological pregnancy)*	- Same age group than cases	- More difficult to approach (visit during evening/week-end)
	- Direct access to the subject (face to face recruitment & blood sampling)	
	- Presumably fecund	- No available serologies (need to store blood samples in separate areas)
	- Regional recruitment	- Link between subjects’ exposures partners’ pathological pregnancy?
	- Large population/easy to match with cases	

According to the TDS hypotheses, TGCT, cryptorchidism, hypospadias and several forms of male infertility are suspected to share common etiological factors [17, 18]. By choosing controls supposed to be fecund or having a normal sperm count, we aim to avoid subjects suffering from a minor form of TDS. In consequence, our controls are likely to be more fertile than the general population of the same age, and may present lower exposure to reproductive toxicants during postnatal periods. This should be taken into account in the interpretation of results when considering adolescent or adulthood exposure. Also, setting up a third control group, more representative of the general population (e.g. by selecting healthy young males from an existing cohort study conducted in France), may be considered.

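### Group B fecundity is inferred only from the partner's pregnancy, so sub-fertile men the design aims to avoid can enter after donor-sperm or male-factor assisted conception

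*Protocol article*

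**What the plan says.** The abstract of the protocol article describes the whole control series as "1000 fertile/fecund controls". The Discussion, in the text following Table 2, gives the reason for choosing controls thought to be fecund or with a normal sperm count: "we aim to avoid subjects suffering from a minor form of TDS". The same paragraph says that testicular germ cell tumours (TGCT) and several forms of male infertility may share causes under the testicular dysgenesis syndrome (TDS) hypothesis.

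The Study population section applies this to the two groups differently:

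- **Group A:** sperm donors, or partners of infertile women, with a measured sperm count above 39 million per ejaculate.
- **Group B:** "Controls of group B are partners of pregnant women hospitalized for a pathological pregnancy", recruited in the regional maternity next to the CECOS. No sperm count, paternity or mode of conception is mentioned.
- **Both groups:** "Controls with a history of cryptorchidism or of TGCT are also excluded". These are the only exclusions specific to controls.

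Table 2 lists "Presumably fecund" among the advantages of Group B. It lists an available sperm count only for Group A. Table 1, which summarises the interview items, names none on how the current pregnancy was conceived.

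**The concern.** The only support for fecundity in Group B is that the man's partner is pregnant. That support is missing in two situations: conception with donor sperm, where the control is not the biological father, and assisted reproduction undertaken because of a male factor. A man below the Group A sperm-count threshold, with no history of cryptorchidism or TGCT, meets the published Group B criteria in either situation.

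If the shared-cause hypothesis is right, such men carry more of the relevant early exposure than other controls and pull the Group B odds ratio towards 1. The article describes no data item that would identify them afterwards, so neither their number nor their influence could be established from what it says is collected.

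**Working it through.** **1. The plan's own figure.** The Determination of the sample size section gives a minimum detectable odds ratio of 1.6 at 10% exposure and 1.5 at 15%, for 500 cases and 1000 controls, with 80% power and 5% significance (taken as two-sided).

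- Case prevalence at p0 = 0.10 and OR = 1.6: p1 = 1.6 × 0.10 / (1 + 0.10 × 0.6) = 0.1509.
- Cases needed with k = 2 controls per case: n = [1.96·√((1 + 1/k)·p̄q̄) + 0.842·√(p1q1 + p0q0/k)]² / (p1 − p0)², where p̄ = (p1 + 2p0)/3 = 0.1170.
- n = (0.772 + 0.350)² / 0.0509² ≈ 485, which is below 500.
- Solved for the odds ratio at exactly 500 cases, the result is 1.59. At 15% exposure it is 1.49.

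Both figures reproduce, with 81% power at the stated odds ratios. The sample size is not in question.

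**2. Dilution.** Let c be the share of Group B men who are sub-fertile. The documents do not give c, so 3% to 10% (15 to 50 of 500 men) is an assumption. As an upper limit on their exposure, give these men the cases' prevalence p1.

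- Group B prevalence: pB = (1 − c)·p0 + c·p1.
- With Groups A and B pooled in equal numbers, replace c by c/2.
- Odds ratio obtained = [p1/(1 − p1)] / [pB/(1 − pB)]. The case odds are 0.1509/0.8491 = 0.1778.

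For c = 3%: pB = 0.097 + 0.0045 = 0.1015, odds 0.1130, OR = 0.1778/0.1130 = 1.57.

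For c = 10%: pB = 0.090 + 0.0151 = 0.1051, odds 0.1174, OR = 0.1778/0.1174 = 1.51.

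| c | OR against B | OR pooled | Power pooled |
|---|---|---|---|
| 0 | 1.60 | 1.60 | 81.2% |
| 3% | 1.57 | 1.59 | 79.9% |
| 5% | 1.56 | 1.58 | 79.0% |
| 10% | 1.51 | 1.56 | 76.8% |

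At 15% exposure and a true odds ratio of 1.5, the range for c = 3% to 10% is 1.48 to 1.43 against Group B and 1.49 to 1.47 pooled.

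**3. Would it show as a difference between the groups?** The cases are common to both comparisons. With matching ignored, the difference in log odds ratios depends only on the two control groups.

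- At 10% exposure each group has about 50 exposed and 450 unexposed men, so SE = √[2 × (1/50 + 1/450)] = 0.21.
- At c = 10% the gap is ln(1.60/1.514) = 0.055, or about 0.26 SE.
- At c = 3% it is ln(1.60/1.573) = 0.017, or about 0.08 SE.

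Neither is detectable.

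**The case against.** The strongest reply is that nothing here is contradictory. The article says Group B is presumed fecund, and its Discussion speaks of controls supposed to be fecund or having a normal sperm count. Two different routes were chosen on purpose because no perfect control group was found. That stands: a reader might infer that the eligibility rules contradict the fertile/fecund description, but they leave a premise unchecked and do not breach a stated rule.

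Other parts of the reply also stand:

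- **Group A is not proven fertile.** Its screen is a single sperm parameter, so it would be wrong to say that sub-fertile men can enter Group B alone.
- **The share is unknown.** Proximity of the maternities to the CECOS makes such couples plausible but does not show how many there are. The article says Group B women are there because pathological pregnancies are managed regionally.
- **A larger effect is not supported.** Giving these men twice the exposure odds of other controls, at a 10% share, would lower 1.6 to 1.47, but this makes them more exposed (18.2%) than the cases (15.1%). Even then the gap between groups is ln(1.60/1.47) = 0.085, about 0.4 SE, with roughly 7% power. A reader might infer a false confounding signal from comparing the groups, but the Statistical analyses section looks for major differences, and this is not one.
- **A hard exclusion has a price.** Cases face no fertility restriction, and the Discussion already concedes that the controls are likely to be more fertile than the general population. Excluding more men moves them further from it.
- **TDS is contested.** The Background calls the concept controversial, and the dilution mechanism depends on it.

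The article also condenses a full protocol that is not shown and may record mode of conception. But the article sets out eligibility in some detail, including a numerical threshold for Group A, and the Group B definition it gives does not secure the property claimed for it.

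**Conclusion.** The point holds as an unenforced premise of modest consequence. The design has chosen fecund controls for a stated reason, and the published Group B definition does not deliver that choice when conception used donor sperm or male-factor treatment. On an assumed share of 3% to 10%, and with exposure capped at the cases' level, a true odds ratio of 1.6 falls by about 0.03 to 0.09 against Group B and by about 0.01 to 0.04 pooled. These figures also take the comparison with fecund controls as the target and accept the shared-cause hypothesis. If either is rejected, the dilution argument weakens, but the unqualified description of the controls in the abstract remains open to correction. The case for acting rests on the low cost and on the lack of any described item that would let the issue be examined later, more than on the size of the bias.

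**What to change.** Ask every Group B man at inclusion how the current pregnancy was conceived: spontaneously, by assisted reproduction for a male factor, by assisted reproduction for other reasons, or with donor sperm. Pre-specify the Group B and pooled analyses restricted to men whose partner conceived without donor sperm or male-factor treatment, and report them beside the unrestricted results. Leave eligibility as it is. If the question cannot be added, state wherever the controls are called fertile/fecund that for Group B this is presumed.

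The cost is one question and a smaller restricted set. On the assumed range, 15 to 50 Group B men drop out of it. Because each case has one Group B control, the same number of matched pairs leaves the Group B analysis, while in the pooled analysis those cases keep their Group A control. Table 2 describes the Group B pool as large and easy to match, so the loss is tolerable. Controls in the restricted analysis will be somewhat further from the general population, a limitation the Discussion already acknowledges; reporting both results lets the reader weigh it.

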### Determination of the sample size

Our research will examine the association between TGCT risk and occupational, domestic and environmental pesticides exposure. Since occupational pesticides exposure is supposed to be less frequent and associated with higher exposure levels than domestic and environmental exposures, we based our sample size calculation on the prevalence of occupational pesticides exposure among case and control parents. Based on the prevalence of agricultural workers in France in 1988 (10%) (http://agreste.agriculture.gouv.fr/IMG/pdf/AGRIFRA07c-2.pdf), the minimum detectable odds ratio with our sample (500 cases and 1000 matched controls) is 1.6, considering a statistical power of 80% at a significance level of 5%. Considering additional occupations associated with pesticides exposure (e.g.: greenhouse worker, sawmill worker, forester), the total prevalence of exposed workers should be higher. Considering a prevalence of exposure of 15%, the minimum detectable odds ratio under the conditions outlined above is 1.5.

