### Statistical analyses

Standard descriptive statistics will be used to describe characteristics and pesticide exposure of cases, controls and mothers/relatives. Exposure variables will be explored using supervised principal component analyses [48]. Risk analyses will be based on conditional logistic regression models, to compute odds ratios for TGCT at different levels of exposure. Exposure variables will be investigated as continuous variables (with appropriate transformation to achieve normality) as well as categorical variables (quartiles or predefined categories depending on variable type). In addition we will create a combined pesticide exposure variable based on pesticide exposure (occupational, environmental and domestic) during prenatal and early postnatal period (PEPPP) and during adolescence (PEA). We will examine PEPPP exposure, PEA exposure, and combined PEPPP and PEA exposure in relation to TGCT risk. The effects of additional potential confounders (other than our matching criteria) on the associations between pesticide exposure and risk of TGCT will be examined and added to the model one by one. Comparison between models with and without adjustment will be used to examine the potential confounding effect of these factors and only factors with relevant changes in the odds ratios will be kept in the final model. Potential confounders include the geographical origin, socio-economic status, tobacco and cannabis consumption, length and weight at birth, birth order, and the familial history of TGCT.

The two control groups will be used first as separate control groups to identify potential major differences. In order to examine whether any of the associations between pesticide exposures and TGCT risk differ by subgroups of known risk factors or by genetic polymorphisms, we will perform additional stratified analyses. Tests for statistical interaction will be used to examine whether any apparent heterogeneity of effect is statistically significant. This will be done by comparing models with and without interaction terms between the risk factor or genetic polymorphisms and the environmental variable (pesticide exposure) with a maximum likelihood ratio test. Sensitivity analyses are planned to explore the impact of potential bias or methodology limitations (such as quality of satellite images, through removing subject born before 1986 having less precise satellite images at time of birth).

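### A history of cryptorchidism excludes controls but not cases, so the prenatal odds ratio is shifted if pesticide exposure and cryptorchidism are associated, and no stated analysis or caveat covers this

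*Protocol article*

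**What the plan says.** The protocol article, under Study population, defines cases by histology and attendance at a participating centre: "Cases are men diagnosed with seminoma or non-seminoma TGCT (ascertained through histological report". No criterion on cryptorchidism is given for them. For controls it adds: "Controls with a history of cryptorchidism or of TGCT are also excluded". Matching is one-to-two: "Two controls (one of each group) are matched to each case on age (±2 years) and the recruiting center".

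The Background introduces testicular dysgenesis syndrome (TDS) as a concept that "proposes that an impaired development of fetal testes may lead to an increased risk of cryptorchidism, hypospadias, testicular cancer and decreased spermatogenesis". It also calls the concept controversial and the biological link between these disorders unresolved. The Objectives place the main interest in prenatal and early childhood exposure.

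The Discussion, after Table 2, gives the reason for the choice of controls: to avoid men with a mild form of TDS. It accepts that such controls may have had less exposure to reproductive toxicants, but speaks only of postnatal exposure and asks for caution only for adolescence and adulthood.

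Statistical analyses does not name cryptorchidism. It plans stratified analyses to see whether associations "differ by subgroups of known risk factors or by genetic polymorphisms", and sensitivity analyses for potential bias, with satellite image quality as the example. Table 1 lists medical history for cases and controls without naming conditions.

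**The concern.** Controls should show how common exposure is in the population that gave rise to the cases. Excluding men with TGCT from the controls follows from the definition of a case. Excluding men with cryptorchidism does not, because cases with that history stay in.

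The exclusion also falls on the pathway that motivates the study. If prenatal exposure raises the risk of cryptorchidism, exposed men are removed from the controls more often than unexposed men, and nothing comparable happens among the cases. The resulting odds ratio matches neither of two interpretable targets: the total effect of exposure, which needs controls with cryptorchidism, or the effect in men without cryptorchidism, which needs the affected cases left out.

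The stated analyses do not resolve this. Groups A and B share the exclusion, so agreement between them is no reassurance. If cryptorchidism is one of the known risk factors meant for stratification, the affected stratum contains no controls. The one caveat in the Discussion leaves out the exposure window of the main objective.

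**Working it through.** **1. The plan's own figure.** Inputs from Determination of the sample size: 500 cases, 1000 controls, 80% power, 5% significance, 10% exposure. The article states: "the minimum detectable odds ratio with our sample (500 cases and 1000 matched controls) is 1.6". A pooled two-proportion calculation (two-sided, two controls per case) gives a minimum detectable odds ratio of 1.590 at 10% exposure and 1.491 at 15%. Both stated values (1.6 and 1.5) reproduce, and the present point does not affect them.

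**2. Effect of the control-only exclusion.** Let c1 and c0 be the probabilities of cryptorchidism in exposed and unexposed men of the source population. The exclusion multiplies the exposure odds among controls by (1 - c1)/(1 - c0), so

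planned OR = total OR × (1 - c0)/(1 - c1).

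The factor is exactly 1 if c1 = c0, above 1 if c1 > c0 and below 1 if c1 < c0.

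**3. Size of the factor.** The article gives neither a prevalence of cryptorchidism nor its association with pesticides, so these are assumed ranges. At 10% exposure:
- exposure-cryptorchidism odds ratio 2: 1.009, 1.018, 1.027, 1.046 and 1.083 at prevalences of 1, 2, 3, 5 and 9%;
- odds ratio 3: 1.017, 1.034, 1.051, 1.085 and 1.155;
- odds ratio 0.7: from 0.997 down to 0.972;
- odds ratio 5 with 9% prevalence, an extreme corner: 1.28.

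If the true total odds ratio is 1, a factor of 1.02 raises the two-sided rejection rate from 5.0% to 5.2%, and a factor of 1.05 raises it to 6.0%.

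**4. The three quantities side by side.** Assume c0 of 2-5%, c1 = 2 × c0, a TGCT risk ratio R of 4-6 for cryptorchidism, and no other effect of exposure. For a rare tumour,

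total OR = [(1 - c1) + R × c1] / [(1 - c0) + R × c0].

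- Low end (c0 = 0.02, c1 = 0.04, R = 4): total = (0.96 + 0.16)/(0.98 + 0.08) = 1.06; factor = 0.98/0.96 = 1.02; planned = 1.08.
- High end (c0 = 0.05, c1 = 0.10, R = 6): total = (0.90 + 0.60)/(0.95 + 0.30) = 1.20; factor = 0.95/0.90 = 1.06; planned = 1.27.
- Affected men left out on both sides: 1.00 in either case.

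With a direct effect of 1.5, c0 = 2%, an exposure-cryptorchidism odds ratio of 2 and R = 4, the total effect is 1.58, the planned comparison gives 1.61, and the symmetric restricted comparison gives 1.50.

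**5. Precision of a restricted analysis.** Leaving out an affected case removes its matched set. If 3, 5, 10 or 15% of sets are lost (485, 475, 450 or 425 cases), the detectable odds ratio becomes 1.60, 1.61, 1.63 or 1.65 at 10% exposure, and 1.50, 1.51, 1.52 or 1.54 at 15%.

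**The case against.** A reader might infer that the prenatal odds ratio is inflated by design. The article does not support that. The shift needs an association between pesticide exposure and cryptorchidism, and the article reports none. It presents TDS as a disputed concept, and an inverse association would push the odds ratio down.

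A reader might also take the whole of 1.08-1.27 as bias because the restricted comparison gives 1.00. In that scenario cryptorchidism lies on the causal path, so most of the excess is real effect: ln 1.06/ln 1.08 and ln 1.20/ln 1.27 are both about three quarters. Measured against the total effect, the distortion is 1.02-1.06, small beside detectable odds ratios of 1.5-1.6.

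Nor does it follow that the restricted analysis should become the main one. The Objectives speak of the impact of exposure on TGCT risk, most naturally a total effect. In the scenarios above, restriction misses that target by more than the planned comparison does (1.00 against 1.06-1.20). If cryptorchidism and TGCT share other causes, conditioning on cryptorchidism may add bias of its own. For the same reason, leaving cryptorchidism off the confounder list is not a fault: a mediator does not belong there when the total effect is sought.

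The choice of controls is also deliberate and explained, a more representative third control group is mentioned as a possibility, and the list of sensitivity analyses is open-ended.

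All of this stands, and it limits the size and certainty of the point. It does not remove the asymmetry. The explanation given does not reach prenatal exposure, and the correction factor cannot be estimated from the study because controls with the history are never enrolled.

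**Conclusion.** The point holds in a conditional form. The eligibility rule is asymmetric. If exposure and cryptorchidism are associated, the prenatal odds ratio equals neither the total effect nor the effect in men without cryptorchidism, and comparing the two control groups cannot reveal it. Under the assumptions in step 4 the total effect is overstated by about 2-6%, and the planned estimate lies 8-27% above the value in men without cryptorchidism. With no association the shift is zero.

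To say that the study estimates no defined effect would go too far. The estimate is the total odds ratio times a factor of known form, and a well-defined contrast remains available because every control is already free of the condition. What is lacking is a stated analysis that uses this, and a caveat for the exposure window the study is mainly about.

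**What to change.** - Keep the analysis with all cases, and label it as asymmetric with respect to cryptorchidism.
- Prespecify beside it an analysis that leaves out cases with a history of cryptorchidism. This compares cases and controls under the same rule, in men without the condition.
- Confirm that the medical history item in Table 1 records cryptorchidism for cases. The second analysis depends on it.
- Extend the Discussion caveat on control selection to prenatal and early childhood exposure, and state that agreement between groups A and B does not address this issue.

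The cost is one further analysis and some precision within it (step 5); the all-case analysis loses nothing. The restricted result omits any effect that runs through cryptorchidism, so it should be read with the all-case result and not replace it.
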